## Problems in Clinical Development for PDS Inner Ear Disorder

PDS is a rare disease, with an estimated patient population of around 4,000 in Japan. The lack of treatment, however, motivates few patients to consult doctors regularly and willingly. Existing reports are limited to those based on limited data collected from outpatients during office visits. Use of existing historical control data on natural course of changes in hearing in PDS therefore is assumed to be insufficient for evaluating the efficacy in clinical research. Newly collecting and accumulating such data would thus contribute to evaluation of efficacy in this trial, and will further serve as basic information in preparing protocols for research to be conducted.

This trial will collect a larger amount of information and more detailed data by measuring objective functions of the inner ear at patients’ homes, in addition to regular office visits, and explore what tests would enable the most precise evaluation. The trial is positioned as Phase I/IIa clinical research aimed at safety analysis and exploratory assessment of efficacy, including endpoints.

# Objective

To explore safety, tolerability, and efficacy of NPC-12T for Pendred syndrome/DFNB4 (PDS), for which treatment has yet to be established

# Study Plan

## Schedule of Activities

Table 1 shows the procedures and schedule of the trial.

Table 1 Procedures and Schedule

|  | Screening | Phase I (3 months) | | | | Phase II (6 months) | | | | | | | | Follow-up | Discontinuation |
| --- | --- | --- | --- | --- | --- | --- | --- | --- | --- | --- | --- | --- | --- | --- | --- |
| **Visits** | Visit 0 (V0) | V1 | V2 | V3 | V4 | V5^1,2^ | V6^2^ | V7^2^ | V8 | V9 | V10 | V11 | V12 | V13 |  |
| **Days/Week** | -2W | D1 | 2W | 4W | 8W | 12W | 14W | 16W | 20W | 24W | 28W | 32W | 36W | 40W |  |
| **Allowable visit windows (days)** | +/-7 | 0 | +/-3 | +/-3 | +/-7 | +/-3 | +/-3 | +/-3 | +/-7 | +/-7 | +/-7 | +/-7 | +/-7 | +/-7 |  |
| In-clinic visits | X | X | X | X | X | X | X | X | X | X | X | X | X | X | X |
| Informed consent | X |  |  |  |  |  |  |  |  |  |  |  |  |  |  |
| Eligibility judgment, random assignment, and prescription of investigational products | | | | | | |  |  |  |  |  |  |  |  |  |
| Eligibility judgment | X | X |  |  |  |  |  |  |  |  |  |  |  |  |  |
| Registration and assignment |  | X |  |  |  |  |  |  |  |  |  |  |  |  |  |
| Prescription of investigational products |  | X | X | X | X | X^1^ | X | X | X | X | X | X |  |  |  |
| Prior medication review |  | X | X | X | X | X | X | X | X | X | X | X | X |  | X |
| Tests to be carried out at subjects’ homes | | |  |  |  |  |  |  |  |  |  |  |  |  |  |
| Instructions on the portable test devices / ePRO | X |  |  |  |  |  |  |  |  |  |  |  |  |  |  |
| Test using the portable devices and ePRO input (at patients’ home) |  |  |  |  |  |  |  |  |  |  |  |  |  |  |  |
| Collection of data from portable devices and ePRO |  | X | X | X | X | X | X | X | X | X | X | X | X | X | X |
| Collection of the portable devices and ePRO |  | X^3^ |  |  |  |  |  |  |  |  |  |  |  | X | X |
| In-hospital tests and observation | |  |  |  |  |  |  |  |  |  |  |  |  |  |  |
| Medical interview on dizziness | X | X | X | X | X | X | X | X | X | X | X | X | X | X | X |
| Thoracic X-ray | X |  |  |  |  |  |  |  |  |  |  |  |  |  |  |
| Pure-tone audiometry | X | X |  | X | X | X |  | X | X | X | X | X | X | X | X |
| Auditory brainstem response | X |  |  |  | X |  |  |  |  |  |  |  | X |  | X |
| Posturography | X | X |  | X | X | X |  | X | X | X | X | X | X | X | X |
| Carolic and c-VEMP tests | X |  |  |  |  | X |  |  |  |  |  |  | X |  | X |
| Speech audiometry | X |  |  |  | X |  |  |  |  |  |  |  | X | X | X |
| Thyroid ultrasound | X |  |  |  |  | X |  |  |  | X |  |  | X |  | X |
| MRI (optional)^4^ |  |  |  |  |  | X^5^ |  |  |  |  |  |  | X^5^ |  | X^5^ |
| Cytology test (optional) |  |  |  |  |  | X |  |  |  |  |  |  | X |  | X |
| Blood collection for generation of iPS cells (optional)^6^ | X |  |  |  |  |  |  |  |  |  |  |  |  |  |  |
| Blood collection for measurement of drug concentration in blood |  |  |  |  |  | X | X | X | X | X | X | X | X |  | X |
| Clinical laboratory tests (blood sampling and urinalysis)^7^ | X | X |  | X |  | X | X | X | X |  | X |  | X | X | X |
| Physical findings (height and weight) | X | X |  |  |  | X |  |  |  |  |  |  | X |  | X |
| Blood pressure, pulse, and temperature | X | X | X | X | X | X | X | X | X | X | X | X | X |  | X |

^1^ The initial administration of investigational products in Phase II for respective subjects shall not be scheduled for the same day.

^2^ The interval between V5 and V6 and between V6 and V7 should be 10 days or more.

^3^ Applies when disqualified by the eligibility judgment.

^4^ An image taken at an external institution may be used if the date of imaging falls within the allowable window and is obtained with the consent of the patient.

^5^ The allowable visit windows are to be four weeks before V5, four weeks after V12, and four weeks after discontinuation. This examination may be performed on an alternative date as an exception.

^6^ If blood was collected in the past for generation of iPS cells, and consent for its use for the clinical trial has been obtained, blood collection need not be newly performed.

^7^ Hematocrit, serum triglyceride, viral tests, thyroid autoantibody tests, pregnancy test are performed at V0 only. Thyroid hormone tests are performed at V1, V5, V12, and discontinuation only.

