Estimated glomerular filtration rate (eGFR) lower than 30 mL/min/1.73 m^2^

7) Immunodeficiency such as HIV or primary immunodeficiency

8) Inability to take investigational products in tablet form, or gastrointestinal dysfunction with risks of malabsorption of sirolimus

9) History of having surgery within eight weeks prior to the registration (any surgery that requires invasion of the body or suture with three or more stitches, including biopsy)

10) Female patients who are pregnant, potentially pregnant, or breastfeeding. Male or female patients who decline to consent to contraception during the trial

Contraceptive methods: Combination of condoms and spermicide; combination of condoms and diaphragms with spermicide; oral contraceptive; intrauterine contraceptive device; or other methods

11) Need to take medications that influence CYP3A4 activation after the administration of investigational products

12) Pulmonary interstitial opacity

13) Diagnosis by the attending physician during the screening phase or from previous observations from hearing tests that the hearing loss is fixed rather than fluctuating

14) Participation in other clinical research and/or trials within six months prior to the date of consent, with the exception of Analysis of Diseases in Otorhinolaryngology Using iPS Cells (approval No. 20140172)

15) Other conditions that the principal investigator or subinvestigator deems inappropriate

[Rationale]

1) through 7), 9) through 12), and 15) To ensure patients’ safety and to assess safety appropriately

8) The situation disturbs prediction of pharmacokinetics of the investigational products.

13) and 14) These may influence analysis of the investigational products.

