# Procedures of the Trial

## Registration of Patients

The principal investigator or subinvestigator will obtain written informed consent from patients who are thought to satisfy the inclusion criteria, or their legally acceptable representatives, and register the patients in accordance with the following procedures:

| 1) Selection of patients | |
| --- | --- |
|  | The principal investigator or subinvestigator will carefully examine whether respective patients are eligible to participate in the clinical trial, taking account of patients’ health conditions, symptoms, age, gender, relationship with the principal investigator, and participation in any other clinical trials. |
| 2) Informed consent | |
|  | The principal investigator or subinvestigator will provide information pertinent to the clinical trial to patients who are thought to satisfy the inclusion criteria of the trial, and obtain written informed consent from the patients or their legally acceptable representatives. |
| 3) Assignment of subject identification code | |
|  | Subsequent to informed consent, required data will be entered into the electronic case report forms, and subject identification code numbers will be assigned. This will be recorded on the subject screening list. The code numbers will be used for identification of the patients throughout this trial. |
| 4) Screening | |
|  | Patients will go through screening two weeks (+/- seven days) before the initial intake of the investigational products. |
| 5) Confirmation of eligibility by the principal investigator or subinvestigator | |
|  | Prior to starting the first dose of the investigational products, the principal investigator or subinvestigator will judge whether patients satisfy the inclusion criteria, based on the assessment during the screening phase, using the eligibility check sheet. |
| 6) Registration of subjects and assignment of investigational products (V1) | |
|  | Patients whose eligibility to participate in the trial is confirmed in 5) will be registered and have investigational products assigned via the electronic case report form. Unique code numbers (pharmaceutical agent numbers) will be assigned to the registered subjects. This will be recorded in the subject screening log.  Patients whose eligibility is denied in 5) will be treated as screen failures. Screen failures will be recorded in the remarks column of the subject screening log. |

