## Procedure for Concealing and Unblinding Randomized Code

The randomization manager will conceal and store the randomization schedule (randomized code) after the random assignment, and unblind it after the database is locked and the trial is completed.

Two sets of emergency key codes will be generated, which will be concealed by the randomization manager. The randomization manager and the emergency contact center (the administrative office supporting clinical trial: Keio University Hospital Clinical and Translational Research Center) will keep them in strict concealment until the appropriate time when the blind is permitted to be broken. When a serious adverse event or other situation demands urgent need for the principal investigator or subinvestigator to access information on assigned treatment to determine treatment of the subject, or when discovery of subject’s pregnancy requires revelation of assigned treatment, the principal investigator will determine whether the code should be partially unblinded. If the principal investigator deems it necessary to unblind the code assigned to the subject in question, the emergency contact center will be requested to allow partial unblinding of the randomization code (emergency key code). The partial unblinding of the emergency key code will be conducted in accordance with the procedure manual for unblinding.

The emergency contact center will communicate the unblinded information to the principal investigator. If partial unblinding is performed, the principal investigator will document justification for unblinding and the extent to which the information is made available.

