# Administration of Investigational Products

Figure 1 Dosing Protocol

Phase I (single-blind): NPC-12T placebo tablets for 3 months (12 weeks)

Phase II (double-blind): NPC-12T active substance tablets or NPC-12T placebo tablets for 6 months (24 weeks)

[Dosage at the outset of the trial]

Subjects weighing less than 40 kg will take one 1-mg tablet orally once every other day.

Subjects weighing 40 kg or more will take one 1-mg tablet orally once per day.

The investigational products are to be taken before sleep.

The bodyweight measured at V1 will be referred to in determining dosage throughout the trial.

<Rationale for the dosing time>

The package insert of Rapamune 1 mg tablets was referred to when setting the dosing time. The insert cites reports that state administration of the tablet after a high-fat meal increased the blood concentration of sirolimus. To reduce effects of high-fat meals, the dosing time of the investigational products is set to be before sleep.

[Prescription of the investigational products]

In Phase I (V1, V2, V3, and V4) and Phase II (V5 and V6), the principal investigator or subinvestigator will prescribe investigational products in accordance with the dosage at the start of the trial described above.

In Phase II (V7, V8, V9, V10, and V11), the unblinded doctor will instruct the principal investigator and subinvestigators on the prescription of the investigational product based on the criteria for dosage change. The principal investigator or subinvestigator will make a judgment on whether dosage reduction is required or dosage increase is permissible, taking account of subjects’ safety, including risks of adverse events. If the conditions are deemed appropriate, the principal investigator or subinvestigator will prescribe the investigational products as instructed by the unblinded doctor. The unblinded doctor will provide instructions to the principal investigator or subinvestigator in accordance with the trough concentration measurements and the prescription schedule generated by the randomization manager. The trough concentration measurements and the prescription schedule are not to be disclosed to any person except the unblinded CRCs until the end of the trial, and will be kept securely locked in a cabinet accessible only to the unblinded doctor.

[Criteria for dosage change]

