### Laboratory Tests

The principal investigator or subinvestigator will perform the following laboratory tests during the screening phase (V0), Phase I (V1 and V3), Phase II (V5, V6, V7, V8, and V12), follow-up observations (V13), and at discontinuation, and record the results on the electronic case report forms.

[Laboratory test items]

| Tests | Variables |
| --- | --- |
| Hematological tests | red blood cell count, hemoglobin, reticulocyte count, white blood cell count, platelet count, lymphocyte count, neutrophil count, and hematocrit (V0 only) |
| Blood biochemical tests | creatinine, ALP (Changes in the level of ALP will be analyzed as a blood marker), total bilirubin, AST, LDH, ALT, BUN, albumin, CRP, total cholesterol, LDL-cholesterol, uric acid, Na, K, Ca, P, Cl, fasting blood glucose, and serum triglyceride (V0 only) |
| Thyroid hormone tests | FT3, FT4, and TSH (all of these are performed at V1, V5, V12, and discontinuation only) |
| Urinalysis | pH, sugar, protein, and occult blood in urine |
| Viral test | HBs antigen, HBs antibody, HBc antibody, HCV antibody, and HIV antibody (all of these will be performed at V0 only) |
| Thyroid autoantibody tests | TgAb, TPOAb, and TRAb (all of these will be performed at V0 only) |
| Pregnancy test | hCG urine (V0 only) |

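### The only pregnancy test is at screening, 88 to 108 days before sirolimus can first be given, and none is scheduled during the 158 to 178 days of Phase II dosing

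*Protocol*

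**What the plan says.** The restriction appears in three places that agree. Footnote 7 of the schedule in the Protocol Summary and footnote 7 of Table 1 (Study Plan) both read "Hematocrit, serum triglyceride, viral tests, thyroid autoantibody tests, pregnancy test are performed at V0 only". The pregnancy row of the table in Section 14.7.3, Laboratory Tests, specifies "hCG urine (V0 only").

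On timing, Registration of Patients states: "Patients will go through screening two weeks (+/- seven days) before the initial intake of the investigational products". The dosing plan under Administration of Investigational Products then begins with "Phase I (single-blind): NPC-12T placebo tablets for 3 months (12 weeks"). Active tablets or placebo follow from V5 for 24 weeks.

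On pregnancy itself, exclusion criterion 10 (Study Population) covers "Female patients who are pregnant, potentially pregnant, or breastfeeding" and also anyone who declines contraception. Section 14.10.9 stops the product at once if a subject is pregnant, and Section 14.11.1 lists pregnancy as a withdrawal criterion. The section on concealing and unblinding the code provides for partial unblinding after a serious adverse event, or "when discovery of subject’s pregnancy requires revelation of assigned treatment". Oversight of Subjects asks for highly effective contraception throughout participation.

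**The concern.** A single screening test could suit a trial in which drug starts soon after screening. Here a 12-week placebo run-in lies between them, so the test guards the start of placebo and not the start of sirolimus. Table 1 marks the eligibility judgment at V0 and V1 only, so nothing re-checks criterion 10 when Phase II product is first prescribed at V5.

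The stop-dosing, withdrawal and unblinding rules all act on a known pregnancy, and after V0 no scheduled procedure would reveal one. A site that follows the plan exactly could start sirolimus in a subject with an unrecognised pregnancy and continue until someone notices. What is at stake is subject safety; no efficacy estimate or power figure is affected.

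Timing a test around the switch was clearly feasible: the same footnote schedules thyroid hormones at V1, V5, V12 and discontinuation.

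**Working it through.** **Inputs.** Visit times and windows are from Table 1, counting days from the first dose at V1 (day 0).

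| Visit | Nominal day | Window | Range |
| --- | --- | --- | --- |
| V0 | -14 | ±7 | -21 to -7 |
| V5 | 84 | ±3 | 81 to 87 |
| V8 | 140 | ±7 | 133 to 147 |
| V10 | 196 | ±7 | 189 to 203 |
| V12 | 252 | ±7 | 245 to 259 |

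**Formulas.** Shortest interval = earliest day of the later visit minus latest day of the earlier visit. Longest interval = latest day of the later visit minus earliest day of the earlier visit.

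**Check against the plan's own figures.** The section on the period for administering the products gives maxima of 178 days for active substance and 259 days for placebo. V5 to V12: 259 - 81 = 178. V1 to V12: 259 - 0 = 259. Both are reproduced, so the windows are being read as the Protocol intends.

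**Intervals under the current plan.**
- V0 test to first possible sirolimus dose (V5): 81 + 7 = 88 to 87 + 21 = 108 days, nominally 84 + 14 = 98. In weeks, 88/7 = 12.6 to 108/7 = 15.4.
- Phase II dosing with no scheduled test (V5 to V12): 245 - 87 = 158 to 259 - 81 = 178 days.
- V0 test to the end of dosing (V12): 245 + 7 = 252 to 259 + 21 = 280 days.

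**Intervals with tests at V5, V8, V10 and V12.**
- V0 to V5: the last test now falls at V5 itself, so the gap to the first sirolimus dose becomes 0.
- V5 to V8: 133 - 87 = 46 to 147 - 81 = 66 days.
- V8 to V10: 189 - 147 = 42 to 203 - 133 = 70 days.
- V10 to V12: 245 - 203 = 42 to 259 - 189 = 70 days.

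The longest interval is 70 days, a cut of 178 - 70 = 108 days (108/178 = 61%). Without V10, V8 to V12 would be 245 - 147 = 98 to 259 - 133 = 126 days.

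**How often this might occur.** The Protocol gives neither the number of women of child-bearing potential nor a pregnancy rate. The following are assumptions: 2 to 10 such women among the 12 active subjects, and 1% to 10% pregnancies per year on contraception. Expected pregnancies = number × annual rate × days/365.

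| Assumption | V0 to V5 | V0 to V12 |
| --- | --- | --- |
| Low | 2 × 0.01 × 88/365 = 0.005 | 2 × 0.01 × 252/365 = 0.014 |
| Middle | 6 × 0.05 × 98/365 = 0.08 | 6 × 0.05 × 266/365 = 0.22 |
| High | 10 × 0.10 × 108/365 = 0.30 | 10 × 0.10 × 280/365 = 0.77 |

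These count all conceptions, including those that would be noticed without a test, so they overstate the number unrecognised at first sirolimus exposure.

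**The case against.** The strongest reply is that this is a consistent design choice. The Protocol manages pregnancy by prevention and response: it excludes those who are or may be pregnant, excludes those who decline contraception, judges eligibility again at V1, brings subjects in every two to four weeks, tells them to report if unwell, and stops dosing when a pregnancy is found. Nothing forbids an unscheduled test. A conception soon after V0 would be about three months along by V5 and might well have been noticed. All of this stands and lowers the probability, but none of it is a scheduled check at or after V5.

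The Protocol also states no fetal risk for sirolimus at this dose. That is correct, and the point does not depend on one. The stated rationale for criterion 10, shared with most other exclusions, is patients' safety and the proper assessment of safety, and pregnancy is placed beside serious adverse events as a ground for unblinding.

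The expected counts rest on assumed inputs and span about 60-fold, and 61% is a reduction in the interval between tests, not in exposed pregnancies. Both remarks are fair; neither number carries the conclusion.

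Finally, only the V5 test follows directly from the gap before first dose, and tests at V12 and discontinuation cannot prevent exposure. The V5 test is indeed the essential part. Repeats at V8 and V10 limit how long dosing could continue undetected, and those at the end of dosing let the follow-up rule in Section 14.10.9 be applied.

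**Conclusion.** The point holds and should be fixed. Three current statements confine the test to V0, and the run-in places that test 88 to 108 days ahead of the first possible sirolimus dose. A further 158 to 178 days of Phase II dosing have no scheduled test. These figures depend only on the Table 1 windows. The 178 days is an upper limit on undetected exposure, since a pregnancy may be noticed sooner.

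The expected number of pregnancies is below one under every assumption tried, so the case rests on how seriously the Protocol itself treats pregnancy and on how little a test would cost. It concerns only subjects of child-bearing potential, and sirolimus exposure only those among the 12 planned for the active arm.

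**What to change.** Amend footnote 7 in both schedule tables and the pregnancy row in Section 14.7.3. For female subjects of child-bearing potential, perform urine hCG:
- at V0, as now;
- at V5, with a negative result required before Phase II product is dispensed;
- at V8, V10, V12 and discontinuation.

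Both tables already mark blood sampling and urinalysis at all of these visits. The visit list in Section 14.7.3 reads "Phase II (V5, V6, V7, V8, and V12), follow-up observations (V13") and so omits V10; add V10 there to match the tables. A positive result is handled under Sections 14.10.9 and 14.11.1 as they stand, and testing both arms alike reveals nothing about assignment.

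The cost is a protocol amendment and four extra strips per eligible subject who completes V12, at most 4 × 16 = 64 if all 16 qualified. No new visit, blood draw or urine collection is needed. The drawback is an occasional withheld Phase II start. Withdrawal is already required once a pregnancy is known, so the test brings that loss forward. It would still matter in a small trial: Section 17.5 conditions its 80% power on 11 evaluable subjects, with 12 planned on active drug, so losing one active subject leaves exactly 11. At a minimum, the V5 test should be added.

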### Expected Duration of the Study

March 2018 through November 2020 (approximately 2.5 years)

Subjects’ registration: March 2018 through December 2019 (approximately 22 months)

### Period for Administering the Investigational Products

NPC-12T tablets (active substance): 178 days maximum

NPC-12T tablets (placebo): 259 days maximum

